### Randomization

Random-number tables are used to allocate subjects to the VA intervention arm, VD arm, VAD arm or the placebo control arm.

### Baseline assessment

The baseline assessment consists of an interview and physical measurement. Baseline fast blood glucose, results of urine toxicology tests, liver function test and other related clinical indexes are obtained by chart review. The baseline interview is conducted prior to vitamin supplementation initiation, and at this visit all subjects are invited to attend VA/D supplementation trial. Following completion of the baseline assessment, participants receive their assignment to one of the four arms.

### Visit schedule and measures

Frequency and length of research visits during the 24 to 32 weeks (according to the anti-tuberculosis drug treatment period) intervention period are the same for subjects in each arm. We standardized the visit schedule to control for any improvement in adherence, possible side effects which might result from VA/VD supplementation alone. We use several measures to assess VA/VD adherence: self-report, pill count, and nursing records of directly observed doses and returned pill boxes.

### Treatment-related side effects

A treatment side effect scale (which measures the degree of VA and/or VD treatment-related side effects) is administered at each monthly visit, and the results are given to medical providers. Side effects include fatigue, irritability, anorexia, headache, fever, insomnia, nausea, vomiting, and other common side effects.

### Sample size and power calculations

We calculated the sample size on the basis of literature research in the related domain and analyzing the objective and indexes in this trial by using formula:

$$N={\left[\left(\left(Z_{\alpha /2}+Z_{\beta }\right)\sigma \right)/\delta \right]}^{2}$$

$$\alpha =0.05\;{\left(Z_{\alpha /2}=1.645\right)}_{,}1-\beta =0.90\;\left(Z_{\beta }=1.282\right)$$

We calculated the needed sample size for the main indexes and selected the largest one. We will need 84 subjects in each arm to have 90% power to show significant difference among trial arms. Considering participants’ compliance, none response and withdraw, a sample size of 100 per arm is needed.

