## Discussion

To our knowledge, this study represents the first randomized controlled trial of a directly observed VA/D supplementation program in active pulmonary tuberculosis patients with diabetes that focused on the contribution of anti-TB and DM treatment effect and the possible mechanisms.

Tuberculosis and diabetes interact with each other, which might make clinical treatment become more difficult than the single disease of pulmonary tuberculosis or diabetes. As diabetes alters immunity to tuberculosis, longer times to culture conversion with treatment, and a higher rate of relapse might result. Treatment failure and death are more frequent in diabetic patients than patients with PTB alone. Alisjahbana reported that in patients with high adherence to treatment, 6-month sputum cultures were positive in 22.2% of patients with diabetes mellitus and in 6.9% of controls and these differences remained after adjustment for age, sex, body mass index, and other factors [15]. In a case–control study [16] treatment failure or death was seen in 41% of the patients with tuberculosis and diabetes mellitus, but in only 13% of those with tuberculosis alone. A recent study by Wang and colleagues [17] discovered that 1-year all-cause mortality was 17.6% in diabetic PTB patients versus 7.7% in non-diabetic controls, and death specifically attributable to pulmonary tuberculosis was significantly more common in diabetic patients (12.2% vs 4.2%).

The most important effector cells for containment of tuberculosis are phagocytes, monocytes and lymphocytes. Diabetes is known to affect chemotaxis, phagocytosis, activation, and antigen presentation by phagocytes in response to M tuberculosis. Vitamin A is an essential micronutrient for a variety of physiological processes, such as tissue differentiation, immunity, and vision. Also, the impacts of VA and retinoids on energy metabolism in animals and humans have been demonstrated in some basic and clinical investigations [18]. Also, it has been proposed recently that vitamin D play a critical role in immunity, respiratory health and insulin resistance. Vitamin A, its metabolites and vitamin D directly inhibit mycobacterial growth in culture [19].

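### The sample-size calculation uses 1.645 as Z(α/2) for α = 0.05 and a formula without the two-sample factor; the stated 90% power at 84 per arm is about 54% for one arm against control, or about 83% for a factorial main effect

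*Protocol article*

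**What the plan says.** Protocol article, section Sample size and power calculations, prints N = [(Z(α/2) + Z(β))σ/δ]². It sets α = 0.05 with "Z_{\alpha /2}=1.645" and takes "1-\beta =0.90\;\left(Z_{\beta }=1.282". On the choice of outcome it says: "We calculated the needed sample size for the main indexes and selected the largest one". The result is: "We will need 84 subjects in each arm to have 90% power to show significant difference among trial arms". The allowance for loss follows: "Considering participants’ compliance, none response and withdraw, a sample size of 100 per arm is needed". Neither δ, σ nor the index that produced the largest N is given.

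The section Planned statistical analyses hypothesises that the arms receiving vitamin A and/or D will do better than the control arm. It names chi-square, F and Kruskal–Wallis tests for comparisons among groups. No one-sided test is mentioned. The Abstract and the section VA/D supplementation scheme describe the trial as a 2×2 factorial. The sample-size section does not say that power refers to the pooled factorial margins.

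**The concern.** Two features of the printed calculation do not fit the comparison that it is meant to support.

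- **The constant.** The subscript is α/2 and α is 0.05, so the value should be 1.960. The printed 1.645 belongs to a one-sided 5% test, or equally to a two-sided 10% test. The tests that the article plans are non-directional.
- **The formula.** As printed, it gives the sample size for one mean against a fixed value. A comparison of two independent arms needs twice that number in each arm. The article speaks of differences among arms and of superiority over the control arm, so a reader will take the 90% to apply to such comparisons.

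This section is the article's only justification for 400 patients. If the 90% is too high, a null comparison with control will be read as stronger evidence against the vitamins than it is. The article also offers itself as a template for other investigators, so the calculation may be copied.

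**Working it through.** **Inputs** (all from Sample size and power calculations): Z(α/2) = 1.645 as printed, Z(β) = 1.282, N = 84 per arm, 100 per arm after the allowance for loss. δ and σ are not given. I take σ as the SD of a single observation and 84 as the output of the printed formula.

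**Step 1. The constants.** The 97.5% normal point is 1.960 and the 95% point is 1.645. The printed Z(α/2) is therefore the one-sided value. Z(β) = 1.282 is correct for 90% power.

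**Step 2. The plan's own figure.** Without δ and σ, 84 cannot be rebuilt independently. Solving the printed formula backwards gives δ/σ = (1.645 + 1.282)/√84 = 2.927/9.165 = 0.319. At this ratio, Φ(0.319 × √84 − 1.645) = Φ(1.282) = 90.0%. So the claimed power appears for a one-sided 5% one-sample test. It also appears for a one-sided 5% factorial main effect, because 0.319/√(2/168) is again 2.927.

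**Step 3. Two-sided 5% power at the same difference.**

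| Comparison | Formula | Power |
|---|---|---|
| One active arm vs control, 84 per arm | Φ(0.3194/√(2/84) − 1.960) = Φ(2.070 − 1.960) | 54.4% |
| Same, 100 per arm, no loss | Φ(0.3194/√(2/100) − 1.960) = Φ(2.258 − 1.960) | 61.7% |
| Main effect, 168 vs 168 | Φ(0.3194/√(2/168) − 1.960) = Φ(2.927 − 1.960) | 83.3% |
| Main effect, 200 vs 200, no loss | Φ(0.3194/√(2/200) − 1.960) = Φ(3.194 − 1.960) | 89.1% |

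Using the t distribution, the first row is 53.9%. If a one-sided 5% test is granted for one arm against control at 84 per arm, power is Φ(2.070 − 1.645) = 66.5%.

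**Step 4. Dependence on the missing inputs.** The 54% does not need δ or σ separately. Whenever n per arm comes from the printed formula, arm-versus-control power is Φ(2.927/√2 − 1.960) = 54.4%. If 84 was rounded up from just above 83, 2.927 becomes at most 2.927 × √(84/83) = 2.945. The figures are then at most about 55% and 84%.

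**Step 5. Numbers needed for 90% two-sided power at δ/σ = 0.319.**
- Arm vs control: 2(1.960 + 1.282)²/0.3194² gives 207 per arm after rounding up.
- Main effect: (1.960 + 1.282)²/0.3194² gives about 103 per cell.

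**Step 6. Differences detectable with 90% two-sided power at 84 evaluable per arm.**
- Arm vs control: 3.242 × √(2/84) = 0.50 SD.
- Main effect: 3.242 × √(2/168) = 0.354 SD.

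**The case against.** The strongest reply concerns the formula. In a 2×2 factorial without interaction, each main effect compares 2n with 2n patients, and the required number per cell is exactly the printed expression. The same expression is right for two arms if σ denotes the SD of a difference. Since the trial is declared factorial, the missing factor 2 may be no error at all.

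This stands in part. It means that the 54% belongs to one comparison, an active arm against control, with σ as the SD of one observation. A reader might infer that 54% is simply the power of the trial; the documents do not support that. But neither of the rescuing readings is stated, and the hypothesis in Planned statistical analyses is framed against the control arm. Nor does either reading repair the constant: with 1.960 in place of 1.645, power under both is about 83% at 84 per arm.

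A reader might also infer that no comparison between arms can reach 90%. That goes too far. If each vitamin adds δ independently (means 0, δ, δ, 2δ), the four-group F test at 84 per arm has 94.7% power. The combined arm against control, now differing by 2δ, has Φ(2 × 2.070 − 1.960) = 98.5%. These figures rest on a largest difference of twice the planning value. If only one arm differs, by δ, the same F test has 54.4%.

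Finally, a reader might extend the point to multiplicity or to yes/no tuberculosis outcomes. The article says that N was computed for several indexes, and a condensed report may leave those details to the full protocol or analysis plan. They are not part of this point.

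**Conclusion.** The calculation is wrong as written. The value given for Z(α/2) is incorrect for α = 0.05. The formula does not match an arm-versus-control comparison unless an unstated definition is supplied. At the implied planning difference of 0.319 SD, two-sided 5% power with 84 per arm is about 54% for one active arm against control and about 83% for a factorial main effect, where the article states 90%. With all 100 per arm evaluable, the figures are about 62% and 89%. For one arm against control, even a one-sided test reaches only about 66%.

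The error in the constant is certain from the page. The percentages rest on three assumptions: that 84 came from the printed formula, that σ is the SD of one observation, and, for the main effect, that the two vitamins do not interact. They describe the index that set the sample size; other indexes needed smaller N and may have more power.

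**What to change.** Keep 400 patients and correct the statement:

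1. Replace 1.645 with 1.960.
2. Name the comparison that the power refers to (each vitamin's main effect, or one arm against control) and print the formula that matches it.
3. State δ, σ (including what it is the SD of) and the index that gave the largest N.
4. If the assumptions above are confirmed, restate power at 84 evaluable per arm as about 83% for each vitamin's main effect, assuming no interaction, and about 54% for one active arm against control. Give the differences detectable with 90% power: about 0.354 SD and 0.50 SD respectively.

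The change is to wording only and needs no extra patients. Its cost is that the published power becomes less favourable, most of all for comparisons of a single arm with control.

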### Planned statistical analyses

We hypothesize that effect of anti-TB and DM treatment in VA and/or VD arms will be better than the effect in the control arm. Descriptive statistics will be calculated and checked for balance in each arm in demographic, physical and other related measurements at baseline. Comparisons among the groups of pulmonary pathological damage, CD_4_^+^ T cell, HOMA-IR, etc., will be performed by Chi-square (categorical variables), F test (continuous variables, normal distribution) or Kruskal–Wallis H test (ranked data). Linear mixed-effects models will be used to analyze the main influencing factors.

We will also calculate anti-tuberculosis and diabetes treatment results, nutritional and immunologic indexes at three time points: before the supplementation (at the inclusion), 2 months after the supplementation, and at the end of the trial (6 to 8 months after the supplementation).

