We designed this VA/D supplementation trial to test the efficacy of micronutrient intervention on active TB patients with DM. We are implementing this randomized controlled trial in a network of TB therapy clinics that offer TB treatment by primary care providers, including standard DM treatment. The primary objective of our trial is to determine whether VA, VD or VAD supplementation is efficacious on anti-tuberculosis treatment and insulin resistance. The secondary objective is to investigate the underlying mechanism including immunological function, nutritional status, etc. We here provide a detailed methodological description of this trial, which can serve as a template for other investigators designing the comprehensive treatment of TB and DM. In addition, we discuss the efficacy of VA and/or VD supplementation on TB and DM to guide future clinical treatment. Finally, we report baseline characteristics of our recruited study population.

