### VA/D supplementation scheme

This is a 2-by-2 factorial-design intervention trial. Active pulmonary tuberculosis patients with diabetes mellitus are offered onsite TB and DM evaluation and treatment by primary care providers, and are free to choose whether to receive VA/D supplementation. Primary care providers receive special training by the project team, including the related knowledge of TB and DM, especially the association between TB and DM; the related nutritional deficiencies and the role of micronutrients in cell-mediated immunity.

Once sign the informed consents, the patients will be randomly assigned to VA (2000 IU daily retinol on top of normal pharmacotherapy) or VD (400 IU daily cholecalciferol on top of normal pharmacotherapy) or VAD (2000 IU daily retinol plus 400 IU daily cholecalciferol on top of normal pharmacotherapy) or control (placebo on top of normal pharmacotherapy) group.

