Vitamin D has been shown to be involved in the host immune response toward Mycobacterium tuberculosis. Recently several VD supplementation trials to active TB patients are available. Administration of four doses of 2.5 mg vitamin D3 significantly hasten sputum culture conversion in patients with the *tt* genotype of the *Taq*I vitamin D receptor polymorphism [24]. However, C Wejse et al. [12] reported that supplementation of three doses of 2.5 mg vitamin D3 at baseline, 5 months, and 8 months did not influence clinical severity score or time to sputum smear conversion in 365 patients in Guinea Bissau. It is possible that the dose used was insufficient. In our trial, we are supplementing VD by daily dose of 2000 IU cholecalciferol, and we are measuring the effect of the supplementation on clinical treatment in active TB patients with diabetes. In addition, prior studies have found that supplementation of VA or VD is associated with improved β cell function or hasten sputum culture conversion, our trial will allow us to determine whether this association will remain true for VA and/or VD use in patients with both TB and DM who have more severe clinical symptom and poorer prognosis, and the underlying mechanism is being investigated.

Despite its strengths, trial limitations should be noted. In our trial, only some doses of VA and VD are observed. However, we designed these doses on the basis of acquiring important information including the VA nutrition status in China by national survey [25], the recommended VA and VD intake formulated by the Chinese nutrition society. Also, abundant literature researches concerning the VA, VD level in the supplementation trials have been implemented. In addition, different distribution of some aspects of the subject in the four arms such as severity of the disease, fundamental nutrition status, socioeconomics status etc. may interfere or reduce our measured effect size. To minimize the differential effect between the four arms, we balanced the four arms regarding age, sex and randomized the subjects to different groups. Furthermore, multivariate logistic regression will be used to identify the measured size to adjust the possible impact factors.

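### The 2×2 factorial trial names four-group omnibus tests as its treatment comparison; these cannot show which vitamin works, in which direction, or that any arm beats control

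*Protocol article*

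**What the plan says.** - **Design** (VA/D supplementation scheme; also the Abstract): "This is a 2-by-2 factorial-design intervention trial". The arms are VA, VD, both (VAD) and placebo.
- **Primary objective** (Background): "to determine whether VA, VD or VAD supplementation is efficacious on anti-tuberculosis treatment and insulin resistance".
- **Hypothesis** (Planned statistical analyses, opening sentence): "We hypothesize that effect of anti-TB and DM treatment in VA and/or VD arms will be better than the effect in the control arm".
- **Planned comparison** (same section): it opens with "Comparisons among the groups of pulmonary pathological damage", goes on to CD4+ T cells and HOMA-IR, and says these "will be performed by Chi-square (categorical variables), F test (continuous variables, normal distribution"). Ranked outcomes get a Kruskal–Wallis test.
- **Models**: "Linear mixed-effects models will be used to analyze the main influencing factors" (Planned statistical analyses) and "multivariate logistic regression will be used to identify the measured size to adjust the possible impact factors" (Discussion).
- **Sample size** (Sample size and power calculations): 84 per arm for 90% power to show a difference among arms, raised to 100 per arm for losses. The formula is printed, but δ and σ are not.

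**The concern.** The objective and hypothesis ask whether VA, VD or their combination is better than control. The named tests ask whether four groups are all alike. With four groups, the F and Kruskal–Wallis tests, and the chi-square test of a binary outcome, have 3 degrees of freedom and no direction. Each can reject because VA differs from VD while neither beats placebo, or because a supplemented arm does worse than placebo.

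If the analysis is run as written, a significant primary result supports no statement about either vitamin until further contrasts are chosen. If those are not fixed in advance, they will be chosen after the data are seen. The article names no VA main effect (VA and VAD against VD and control), no VD main effect, no VA-by-VD interaction and no contrast of a named arm with control.

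**Working it through.** **1. What each stated element can answer.**

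| Element | Question it answers |
|---|---|
| Primary objective | Does VA, VD or VAD work? |
| Hypothesis | Are the supplemented arms better than control? |
| Chi-square, F, Kruskal–Wallis among groups | Does any arm differ from any other, in either direction? |
| Linear mixed model | Which influencing factors matter? Treatment terms are not named |
| Logistic regression | Adjustment for possible impact factors; treatment terms are not named |

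No row in the lower part answers a question in the upper part. This holds at any effect size.

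**2. The plan's own figure.** The printed formula is N = [(Z_α/2 + Z_β)σ/δ]², with 1.645 and 1.282. It cannot be run forward because δ and σ are not given. Solved backwards at N = 84:

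- As printed: δ/σ = √[(1.645 + 1.282)²/84] = √(8.567/84) = 0.319
- With 1.960, the two-sided 5% value: 0.354
- With the factor 2 for comparing two arms, and 1.645: √(2 × 8.567/84) = 0.452
- With both changes: 0.500

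The effect size is therefore an assumption, and the range 0.319 to 0.500 is carried forward.

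**3. Power with one active vitamin and no interaction.** Write d = δ/σ and n = 84 per arm, with 4 × 84 − 4 = 332 error df and a two-sided 5% level. The cell means in SD units are 0, d, 0, d.

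- Omnibus F: non-centrality n × Σ(μ − mean)² = 84 × 4 × (d/2)² = 84d², on 3 df. At d = 0.319 this is 8.57.
- Main effect (168 against 168): non-centrality d²/(1/168 + 1/168) = 84d², on 1 df.

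The non-centrality is the same, but the F test spreads it over three degrees of freedom.

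| δ/σ | Omnibus F | Main effect, α 0.05 | Main effect, α 0.025 |
|---|---|---|---|
| 0.319 | 68% | 83% | 75% |
| 0.354 | 78% | 90% | 84% |
| 0.452 | 95% | 98.5% | 97% |
| 0.500 | 98% | 99.5% | 99% |

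The last column is the stricter Holm step when two main effects are tested. A single active arm against control (84 against 84) has 54% power at 0.319 and 90% at 0.500.

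**4. Other patterns at d = 0.319.** The cell order is control, VA, VD, VAD.

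| Pattern | Cell means | Omnibus F | Each main effect, α 0.05 |
|---|---|---|---|
| One vitamin active | 0, d, 0, d | 68% | 83% |
| Both, additive | 0, d, d, 2d | 95% | 83% |
| Fully sub-additive | 0, d, d, d | 54% | 31% |
| Only the combination works | 0, 0, 0, d | 54% | 31% |

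In the last two patterns each main effect is d/2. Its non-centrality is 84 × (d/2)² = 2.14, which gives 31%. For the F test the non-centrality is 84 × ¾d² = 6.43, which gives 54%.

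**The case against.** The strongest reply has four parts.

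- **The text is condensed.** An F test can come from a two-way analysis of variance, the mixed model could carry VA and VD terms, and contrasts are often left to an analysis plan. This stands as far as it goes: a reader might infer that main effects are excluded, or that the mixed model is barred from estimating treatment effects, and the article says neither. But it does name the comparison as one among groups and sets the F test beside chi-square and Kruskal–Wallis, which reads as a four-group comparison. The point concerns that stated method, not missing detail.
- **The questions are about arms against control, and the sample size is set per arm.** This stands. The VA margin is not literally the stated hypothesis, because half of its comparator receives VD. It is also why VAD against control cannot be treated as a side question when the primary objective names VAD. It does not rescue the omnibus test, which makes no contrast with control either.
- **The power gain is not free.** This stands. Holm over two factors cuts the 0.319 SD advantage from about 15 points to about 7 (75% against 68%), and testing more primary outcomes lowers the main-effect power further.
- **The omnibus test rejects more often in three of the four patterns shown.** This is true at 0.319 SD, although even then it does not say which vitamin is responsible.

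**Conclusion.** The concern holds as a mismatch between the stated tests and the stated hypothesis. In a declared factorial trial, the named group comparison cannot attribute an effect to VA or VD, give its direction, or show that any arm beats control. That conclusion needs no assumption about effect size.

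The power argument is secondary and conditional. A reader might infer that the plan discards a large amount of power that a factorial analysis would recover at no cost. The documents do not support that. The 15-point difference requires 0.319 SD (back-solved from a formula that lacks the two-arm factor and labels 1.645 as Z_α/2 at α = 0.05), exactly one active vitamin, no interaction and no multiplicity correction. At 0.50 SD the difference is under 2 points. Under sub-additive or combination-only effects at 0.319 SD it reverses, 31% against 54%. All these figures assume 84 evaluable patients per arm and a continuous, normally distributed outcome with equal variances.

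**What to change.** Under Planned statistical analyses, make the confirmatory analysis one model per primary outcome (linear, logistic or ordinal according to the outcome) with terms for VA (yes/no) and VD (yes/no). Then:

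- report the two main effects with 95% confidence intervals, and state the multiplicity control across the primary tests;
- report the VA-by-VD interaction and the four cell estimates alongside, because main effects are diluted when effects are sub-additive or confined to the combination;
- pre-specify the contrasts of VA, VD and VAD with control, and give VAD against control a standing that matches its place in the primary objective;
- keep the chi-square, F and Kruskal–Wallis comparisons as descriptive;
- state whether the mixed and logistic models are the ones that carry these treatment terms.

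The cost is wording only: no added patients, visits or data. The article reports 37 of a planned 400 enrolled, so the change could be made before outcome data are analysed. The statistical price is the multiplicity adjustment and the weak main effects under a strong negative interaction or a combination-only effect, which is why the interaction and the simple effects must be reported.
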